1. GPA
2. Use of mental/behavioral health services
3. Enrollment status, including leaves of absences and withdrawals from school

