#### Part B. Intervention:

Inclusion criteria:

1. 18-25 years old.
2. Enrolled in undergraduate program at the college or university where the intervention takes place.
3. Students who endorse delusion-like experiences (DLEs): PDI score  $\geq 4$ .
4. Students with mild to moderate depressive symptoms: BDI score  $\geq 6$ .

Exclusion criteria:

1. Inability to provide informed consent.
2. Not proficient in English.
3. Current DSM-V diagnosis with active symptoms (such as active psychotic symptoms, current suicidality, serious active alcohol or substance use, marked deterioration in functioning over the prior month) determined by clinical interview with participant, or self-report of a psychiatric diagnosis that necessitates close monitoring or individual therapy and/or inpatient or partial hospitalization.
4. Current enrollment in psychological or behavioral health treatment.
5. Current use of psychotropic medications (other than stimulants) prescribed by a physician.

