### 5) Study Procedures

#### Part A: On-campus screening

##### Screening:

Interested students will be given a consent form (**Consent form A**), discuss the consent form and receive answers to any questions with a member of the study team, and, if interested, that member of the study team will obtain informed consent. Consent form A also includes information about longitudinal follow-up questionnaires. These may be sent via an MGB secured link every six months. If the subject completes these questionnaires, they will receive additional compensation. They will also be able to grant permission for the study team to access and obtain information from their college records (including GPA, enrollment status, and use of behavioral health services). Academic information will be collected through the school longitudinally for students from Part A who grant permission in the consent form.

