### Longitudinal Follow-Up:

Participants who completed Part A of the study will be asked to complete online questionnaires every six months for up to two years following the intervention. If they agreed to the collection of academic information in Consent A, a member of the study team will work with the local college/university to obtain this information. Participants will be mailed \$10 in the form of a check for each online follow-up assessment they complete. The assessment will be the same as the initial survey battery. A member of the study team will review the participants' scores for potential safety concerns within 24 hours following a survey submission.

If a participant indicates mild suicidal ideation (BDI #9 Suicide Item = 1, which is endorsed by 10-15% of the college student population nationwide) and moderate depressive symptoms (BDI total score = 19-29), [name], the PI of the study, will be notified, and a member of the study team will reach out to that participant via phone and/or email in order to provide an assessment via phone or in person. See below \* for potential outcomes and actions that may follow this assessment. At minimum, the study team member will provide the student with a list of mental health resources and discuss with the participant a plan in case their symptoms worsen.

In the event the student endorses 2 or higher on the BDI #9 Suicide Item (indicating suicidal ideation with intent) or a 1 on the BDI #9 item and severe depressive symptoms (BDI total score > 29), [name], the PI of the study, will be notified, and a member of the clinical study team will contact the student via phone and/or email in order to provide an assessment via phone or in person. In the event that the student does not respond, the University will be informed about the scores of the student and may contact them.

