\* In accordance with clinical practice, if the study clinician determines there is clinically significant suicidality on further evaluation, they will recommend appropriate steps. This may range from contacting other treaters, if any; arranging for an urgent appointment at the University or College counseling program; or referring the student to a local emergency service such as the Acute Psychiatry Service at MGH. Depending on the nature/level of the risk and the student's ability to comply with recommendations, the study clinician may also need to issue a Section 12 that authorizes emergency transport to and evaluation in an appropriate facility. Study participants will be informed of the risks associated with study participation including the possibility that in the event that there is concern about a serious risk of suicidality (or harm to others), participants' private information may need to be shared in order to ensure his or her safety. These procedures are clearly described in the consent forms.

For academic information, participants must sign a separate section of Consent form B. This is asking for permission to obtain, in collaboration with each university, academic information for the participants. All information obtained through the school registrar and counseling center. The following measures will be obtained via the college of enrollment every 12 months for those who have given written permission.

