### **6) Biostatistical Analysis**

To measure the feasibility and acceptability of the prevention program (Aim 1), we will conduct qualitative and quantitative analyses of the recruitment and retention of participants to the RT Intervention. We will report descriptive statistics of those who participated in the RT group and compare them to those who were offered the group and declined. In addition, we will conduct analyses of the knowledge, feasibility, and acceptability measures to determine whether the RT Intervention increased participant's knowledge base of resilience-promoting tools and behaviors. To measure the efficacy of the program (Aim 2), we will conduct repeated measures analysis of variance (ANOVAs) to determine whether the RT Intervention leads to improvement of symptoms (i.e., psychotic experiences, depression and anxiety, the primary outcomes), social functioning/processing, and resilience, compared to the WLC condition. In addition, we will utilize linear and logistic regression to examine potential moderators to treatment response. To measure the impact of the program on long-term outcomes (Aim 3) we will conduct linear regressions using a dichotomous responder variable to regress on the psychological, social, and school functioning variables over time. Further exploratory longitudinal analysis will be conducted with hierarchical linear regression (HLM) to examine person-level variables that may impact long-term outcomes. Finally, multiple regression analyses will be conducted to identify predictors of symptom change and long-term outcomes (Aim 4).

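### Aim 3 applies linear regression to school outcomes that include a categorical enrollment status and that, for GPA and campus service use, can be observed only while a student is enrolled

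*Protocol*

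**What the plan says.** **Who enters.** Section 3, Part B, requires age "18-25 years old" and "Enrolled in undergraduate program at the college or university where the intervention takes place". The screening criteria are parallel. Neither part sets a class year or a minimum remaining time at the college, so final-year students are eligible.

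**What is collected.** Section 5, Longitudinal Follow-Up, lists three academic measures: GPA, use of mental health services, and "Enrollment status, including leaves of absences and withdrawals from school". On source and timing it says: "The following measures will be obtained via the college of enrollment every 12 months for those who have given written permission". The school's registrar and counseling center are named as the suppliers. Graduation is not mentioned anywhere in the protocol.

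**For how long.** Participants are "asked to complete online questionnaires every six months for up to two years following the intervention". That limit is written for the questionnaires. For school records the screening text says only: "Academic information will be collected through the school longitudinally for students from Part A who grant permission in the consent form". No end date is given.

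**How it is analysed.** Section 6 assigns Aim 3 to "linear regressions using a dichotomous responder variable to regress on the psychological, social, and school functioning variables over time", with further exploratory hierarchical modelling. School functioning is one of Aim 3's three long-term domains, beside psychological and social functioning.

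**The concern.** The named method and the data do not match in two respects.

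First, enrollment status is a set of states: enrolled, on leave, withdrawn and, in practice, graduated. A linear regression needs a numeric scale, and these states have none. Graduation is a good ending and withdrawal a poor one, yet both leave the student off the roll.

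Second, a college can supply a GPA or a counseling record only for time in which the student is there. After graduation, or during leave or withdrawal, there is no new GPA, and a blank counseling record shows absence rather than lack of use. If such zeros enter the regression as non-use, differences in service use shrink. If class year is also related to being a responder, the comparison can be biased in either direction.

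At stake is the reading of one secondary domain: whether responders go on to do better at school.

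**Working it through.** The protocol states no class-year mix, graduation rate or expected missingness, so there is no figure to reproduce. The question is how large the affected share could plausibly be.

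**Assumptions, none from the documents:** a four-year program; on-time graduation; academic records pulled at months 12 and 24; four illustrative class mixes. For person-time, fourth-years graduate 8 months after a fall entry or 3 months after a spring entry, and third-years 12 months later than that.

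**Formulas**, with y3 and y4 the shares of third- and fourth-years at entry:
- graduated by month 12: g12 = y4
- graduated by month 24: g24 = y3 + y4
- share of the two pulls that fall after graduation: (g12 + g24)/2
- share of 24-month person-time enrolled: sum over class years of share × min(24, months to graduation)/24

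| Mix, years 1/2/3/4 (%) | g12 | g24 | Pulls after graduation | Person-time enrolled, fall / spring entry |
|---|---|---|---|---|
| 25/25/25/25 | 25% | 50% | 37.5% | 79% / 69% |
| 40/30/20/10 | 10% | 30% | 20% | 90% / 84% |
| 60/20/15/5 | 5% | 20% | 12.5% | 94% / 90% |
| 10/20/30/40 | 40% | 70% | 55% | 68% / 54% |

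Example, uniform mix, fall entry: 0.25 × (8/24 + 20/24 + 1 + 1) = 0.79.

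**How much is truly empty.** A pull after graduation is not necessarily blank. A student who graduates between months 12 and 24 has part of a year of records. The whole second-year interval is empty only for those who graduated by month 12, that is g12: 25% if uniform, 5-40% over the mixes.

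**Effect on service use.** If a share e of students has no enrolled time in the interval and is read as non-use, a true rate u is seen as u × (1 − e). Take assumed second-year rates of 20% and 12% in two groups with the same e. With e = g12 = 25%, they are read as 15% and 9%, so a difference of 8 points becomes 6. Over e = 5-40% the difference becomes 8 × 0.95 = 7.6 to 8 × 0.60 = 4.8 points. This counts only wholly empty intervals; partial years dilute it further.

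**Method against variable.** Of the three measures, GPA is the only one plainly numeric. Service use is naturally a count or a yes/no over time at risk, and status is a category. Section 6 names one class of model for all of them.

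**The case against.** The strongest reply is that most of this is detail for a statistical analysis plan, which is not at hand. Coding of states, restriction to enrolled time and treatment of absent GPA commonly sit there. The status item opens its list with *including*, so graduation is not excluded, and a registrar can report it. The screening section allows optional self-reported academic information. The demographics form may already hold class year. GPA may mean cumulative GPA, in which case a student who leaves keeps a last value.

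Much of that stands. The lack of a graduation code would not, alone, be a finding. What remains is a stated choice: the protocol names linear regression for school variables, one of which is categorical and another of which depends on time at the college. The exploratory hierarchical models do not change this, since they are aimed at person-level predictors.

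Three stronger readings are tempting, and the documents do not support them.

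- *Students who withdraw or take leave cannot be scored.* They can: those events are named as part of the enrollment outcome. Only their GPA for the period and their campus service use are unobservable.
- *Much of the two-year school data is structurally empty.* No figure in the documents supports this. The two-year limit is written for the questionnaires, and extending it to school records is an inference. Many later pulls would hold partial records.
- *Pooling graduates with withdrawals destroys the comparison.* Assume 100 students per group, leave or withdrawal of 10% against 5% among non-graduates, and half graduated. Pooled, the rates are 55% and 52.5%, with z = 0.025/√[(0.55×0.45 + 0.525×0.475)/100] = 0.35. With graduation counted as favourable they are 5% and 2.5%, with z = 0.93. The information ratio is (0.93/0.35)², about 7. With the 40/30/20/10 mix, z is 0.52 against 1.11, a ratio of about 4.6. Taking 100 non-graduates per group (z = 1.35) as the reference would give about 14 and 7, but that blames the coding for a loss that comes from having fewer students at risk. In any case the rates are invented, and nothing in the protocol says that graduates will be pooled with withdrawals.

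**Conclusion.** The point holds in limited form. Linear regression does not suit enrollment status, and GPA and campus service use should not be analysed as if observable throughout follow-up in a population open to every class year.

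The share affected is unknown from the documents. Under the assumptions above it is unlikely to be trivial: even the mix most weighted to first-years has 20% graduated by month 24. The range across mixes is too wide for any single figure to be quoted as the size of the problem.

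The consequence is confined to one secondary domain of Aim 3. The primary outcomes are psychotic experiences, depression and anxiety. The Aim 3 analysis is by responder status rather than by randomised group, and waitlisted students are due to start the training after about four weeks. The randomised comparison is therefore not touched.

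**What to change.** In section 5, Longitudinal Follow-Up:
- Record graduation as a separate enrollment state, and ask the registrar for the terms enrolled in each 12-month interval.
- Capture class year or expected graduation date at screening if the demographics form lacks it.

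In section 6, Aim 3:
- Make the enrollment outcome leave or withdrawal without a degree, count graduation as favourable, and analyse it by logistic rather than linear regression.
- Analyse campus service use over enrolled time only, with a rate model and enrolled terms as offset.
- Analyse GPA over enrolled time only, and say whether it is term or cumulative. Report it beside the enrollment outcome, because restricting to enrolled time still selects students who stayed.

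Cost: protocol wording, at most one form item, a slightly fuller record request and a little more analysis work. The stated school-outcome sample at later pulls will be smaller. No additional visits or students are needed.

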### Research Electronic Data Capture (REDCap):

For the online follow-up assessments, students will receive an individual secure link (with a unique username to enter their data) to the questionnaires on REDCap (Research Electronic Data Capture) every

## PROTOCOL SUMMARY

six months for two years following the screening. The online follow-up assessments will begin within two months after the completion of the RT intervention. These self-report measures will be collected using REDCap (Research Electronic Data Capture), a platform for electronic data capture that streamlines data collection and management, and ensures data integrity, resulting in improved data quality. The REDCap software allows researchers to design and implement study surveys for collecting, storing, retrieving, and manipulating data electronically. Participants will enter survey responses into electronic assessment forms, and the responses are then transmitted securely via encrypted connection and stored in a secured database. This electronic data capture eliminates the need for subsequent data entry by staff, thus minimizing human error. For this study, participants will complete the electronic assessments on their own computer terminals, under specific usernames sent by the Research Assistant in individually addressed e-mails. Using 128 bit RSA Secure Socket Layer (SSL) encryption, pre-determined users will log in to the questionnaires using secured browsers behind the MGB Healthcare Systems IS corporate firewall. Participants will be e-mailed a unique identifying key that will link them to various electronic forms. Therefore, each student/subject will only have access to his or her own survey data.

Data will be stored automatically and securely on an MS SQL Server, accessed over industry standard SSL 128 bit RSA encryption during data transfers. Data is routinely backed up locally onto a redundancy server and stored in a separate database. Long term storage on MGB servers occurs nightly and allows for incremental backup over multiple systems. Therefore, should one drive be physically damaged, there will be multiples within the chain to replace it. Both data servers are stored within MGB IS corporate firewall, in a secure, key access facility with password-protected computers. Only vetted MGB IS security officials will have access to physical machines storing study data. Since data are stored on a protected server, a compromise of any individual computer at a research facility will not lead to a breach of the secure database. Individual computers designated for data capture do not store participants' identifying information or study data.

### **6) Biostatistical Analysis**

To measure the feasibility and acceptability of the prevention program (Aim 1), we will conduct qualitative and quantitative analyses of the recruitment and retention of participants to the RT Intervention. We will report descriptive statistics of those who participated in the RT group and compare them to those who were offered the group and declined. In addition, we will conduct analyses of the knowledge, feasibility, and acceptability measures to determine whether the RT Intervention increased participant's knowledge base of resilience-promoting tools and behaviors. To measure the efficacy of the program (Aim 2), we will conduct repeated measures analysis of variance (ANOVAs) to determine whether the RT Intervention leads to improvement of symptoms (i.e., psychotic experiences, depression and anxiety, the primary outcomes), social functioning/processing, and resilience, compared to the WLC condition. In addition, we will utilize linear and logistic regression to examine potential moderators to treatment response. To measure the impact of the program on long-term outcomes (Aim 3) we will conduct linear regressions using a dichotomous responder variable to regress on the psychological, social, and school functioning variables over time. Further exploratory longitudinal analysis will be conducted with hierarchical linear regression (HLM) to examine person-level variables that may impact long-term outcomes. Finally, multiple regression analyses will be conducted to identify predictors of symptom change and long-term outcomes (Aim 4).

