### 1) Background And Significance

Our group, the MGH Resilience and Prevention Program (RAPP) <https://www.resilienceandprevention.com>, has developed a brief behavioral intervention, called “Resilience Training” (RT), that is modeled on established, evidence-based treatments for treating psychiatric illnesses. The goal of RT is to help young people who may have one or more risk factors for psychiatric illnesses develop more effective coping skills for managing stress – particularly stress caused by challenging social interactions and negative emotions. RT is referred to as a “workshop” or “training”, because it is focused on the *prevention* of psychiatric illness, rather than treatment of clinically established conditions. These trainings or workshops are administered by two clinicians (or a clinician and a clinician-in-training) to groups of 8-14 participants. In each session of RT, the leaders teach techniques that increase well-being and mindfulness and improve social functioning and emotion regulation capacity. The emphasis of the program is on enhancing existing strengths and coping skills (rather than on “fixing” deficits or “treating” symptoms), so that trainees are better able to weather the stresses and adversities that inevitably arise in people’s lives.

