Control Group: After an initial piloting phase of the intervention, a waitlist control (WLC) group will be added to the study design. Half of the enrolled students (randomly selected during the pre-workshop/baseline assessment) will be selected for Group 1, which starts immediately following session B1, while the other half (Group 2) asked to wait for one round (approximately 4 weeks) before starting the RT intervention. The WLC students will complete the initial assessments at the same time as the students who will receive the RT intervention immediately and will also complete assessments before and after the 4-week intervention they complete. Thus, the WLC participants will undergo three assessments following the screening, rather than the two assessments (before and after the intervention) that the first group of students will complete. Although exclusionary criteria for Part B include current enrollment in psychological or behavioral health treatment, students in the WLC group will not be dissuaded from seeking treatment during the waitlist period, and eligibility for Part B will be reassessed prior to their enrollment in the intervention.

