### RT Intervention:

This intervention is comprised of techniques derived from established treatments of psychiatric illnesses including: mindfulness, Cognitive Behavioral Therapy (CBT), Mindful Self-Compassion (MSC) therapy and Mentalization Based Treatment (MBT). The RT intervention begins with an introduction to the concepts of resilience and mindfulness; mindfulness techniques are taught and emphasized throughout the program. The RT intervention consists of four (4) weekly sessions. Each intervention group will have approximately 8-14 participants.

The intervention combines these modalities during the course of the four sessions, in the following manner: The first session will introduce the concept of resilience and mindfulness and the practice of mindfulness; the second session will then introduce MSC concepts and skills; the third and fourth sessions will introduce mentalization skills and integrate all of the modalities, using simulated (film clips) and real life examples provided by participants, to facilitate the implementation of the concepts and skills in everyday life. Participants will also be given short homework assignments after each session to help them use the skills and understand their benefits.

Intervention materials may be provided to the participants during the workshops to enhance their learning, however, no additional assessments will be administered during the four sessions of the RT intervention.

In order to assess and maintain fidelity to the intervention manual across iterations of the intervention, the leaders of the group may audio record each intervention session. Members of the clinical study team who have not led the intervention will then listen to a portion of these recordings and rate the sessions based on predetermined adherence criteria. Subjects will be informed of the potential for audio recordings of sessions for only this purpose prior to consenting to Part B. Recordings and recording devices will be stored behind locks and/or encryption in order to ensure subject privacy. Fidelity ratings will be made according to the RT Adherence Measure.

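### The repeated-measures ANOVA named for Aim 2 has no term for RT workshop group, so type I error exceeds nominal if outcomes correlate within groups

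*Protocol*

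**What the plan says.** Section 6 of the protocol (Biostatistical Analysis) fixes the Aim 2 method: "we will conduct repeated measures analysis of variance (ANOVAs) to determine whether the RT Intervention leads to improvement of symptoms". The symptoms are "psychotic experiences, depression and anxiety, the primary outcomes", and the comparator is the waitlist. The same sentence covers social functioning and resilience. Hierarchical linear modelling appears once in that section. It is reserved for exploratory longitudinal work on person-level variables and is not assigned to Aim 2 or to workshops.

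Three other places describe the design:

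- **Delivery.** RT is "administered by two clinicians (or a clinician and a clinician-in-training) to groups of 8-14 participants" (section 1). The RT Intervention part of section 5 repeats the size: "Each intervention group will have approximately 8-14 participants". Later sessions teach by "using simulated (film clips) and real life examples provided by participants".
- **Allocation.** "Half of the enrolled students (randomly selected during the pre-workshop/baseline assessment) will be selected for Group 1" (section 4), so the student is the unit of randomisation and the ratio is 1:1.
- **Control.** Group 2 is "asked to wait for one round (approximately 4 weeks) before starting the RT intervention". No group activity is described for the wait.

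The protocol never mentions workshop group or leader as an analysis factor. It states no ICC, alpha, sample size or number of groups.

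**The concern.** Students in one workshop share two leaders, the same peers and each other's examples, so their changes from baseline may be correlated. The leader pair can also differ in seniority between workshops. The protocol plans adherence ratings to keep delivery consistent between iterations, which recognises that workshops may differ. Waiting students have no such shared exposure. This is individual randomisation with clustering in one arm only.

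A repeated-measures ANOVA with arm as the between-subject factor has a between-subject and a within-subject error term. Neither contains a workshop component, so each RT student counts as a full independent unit. If there is positive correlation, the intervals for the RT effect on PDI, BDI and STAI are too narrow and the p-values too small. One unusually good or poor workshop could then pass for an effect of RT. The same applies to every other Aim 2 outcome analysed this way.

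**Working it through.** The protocol states no sample size, power or alpha, so there is no figure of its own to reproduce.

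**Inputs from the protocol:** group size m = 8 to 14; allocation 1:1; clustering in the RT arm only.

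**Assumptions:** two-sided alpha 0.05; ICC ρ of the change scores from 0 to 0.10; equal variances and equal arm sizes n.

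**Step 1.** With a baseline and one post assessment, the ANOVA arm-by-time F equals the square of the two-sample t on change scores. The error rate can therefore be worked out for the t test.

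**Step 2.** The naive variance of the difference is 2σ²/n. The true variance is (σ²/n)[1 + (m−1)ρ] + σ²/n. Their ratio is R = 1 + (m−1)ρ/2.

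**Step 3.** The actual type I error is 2[1 − Φ(1.96/√R)].

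At ρ = 0.05:

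- m = 8: R = 1 + 7 × 0.05/2 = 1.175; √R = 1.084; type I error 7.1%.
- m = 14: R = 1 + 13 × 0.05/2 = 1.325; √R = 1.151; type I error 8.9%.

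| Assumed ICC | True SE / naive SE, m = 8 | True SE / naive SE, m = 14 | Type I error, m = 8 | Type I error, m = 14 |
|---|---|---|---|---|
| 0 | 1.000 | 1.000 | 5.0% | 5.0% |
| 0.01 | 1.017 | 1.032 | 5.4% | 5.7% |
| 0.02 | 1.034 | 1.063 | 5.8% | 6.5% |
| 0.05 | 1.084 | 1.151 | 7.1% | 8.9% |
| 0.10 | 1.162 | 1.285 | 9.2% | 12.7% |

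**Step 4, simulation check.** There were 20,000 runs per setting, with m = 8 and 14 and an assumed 3, 6 or 10 RT groups. At ICC 0.05 the unadjusted test rejected in 6.8%-7.2% of runs for m = 8 and 8.5%-9.0% for m = 14, in line with the formula. A partially nested test (RT group means against individual waitlist students, Satterthwaite degrees of freedom) rejected in 4.7%-5.4% with 6 or 10 groups and in 5.3%-6.7% with 3. These ranges run over ICC 0 to 0.10.

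**Step 5, where the random effect must act.** Baseline precedes the workshop, so clustering arises in the change. If a workshop intercept u is added equally to the pre and post scores, then (post + u) − (pre + u) = post − pre, and u drops out of the arm-by-time contrast. In four simulated data sets (6 groups of 11, clustering at post only), a mixed model with such an intercept gave SEs of 0.183, 0.197, 0.189 and 0.221. The unadjusted SEs were 0.182, 0.197, 0.189 and 0.221. SEs based on group means were 0.291, 0.322, 0.255 and 0.406. The time-constant intercept corrected essentially nothing.

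**The case against.** The strongest reply is that section 6 is one paragraph naming model families for four aims. It never says that students are treated as independent. Random terms and degrees of freedom are often left to an SAP, which may exist and is not shown, and a nested workshop factor can be fitted within an ANOVA framework. This stands in part: the independence assumption is inferred from the model named, not stated. But the protocol does name a model, and its ordinary form has no workshop term. The one multilevel method it mentions is assigned to a different purpose. Following the text as written would omit the workshop.

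The second reply is that the ICC may be negligible. That is fair. At ICC 0 there is no inflation, and at 0.01 the error is only 5.4%-5.7%.

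A reader might also infer several stronger points that the protocol does not support:

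- **That type I error is certain to exceed 5%.** The excess depends on a positive ICC, and neither the ICC nor alpha is given.
- **That the usual two-arm design effect applies.** At ICC 0.05 it would give 9.2%-12.7%, but waiting students are ungrouped, so 7.1%-8.9% is the relevant range.
- **That having few workshops makes the unadjusted error much worse.** The simulation with 3 to 10 groups shows no consistent excess over the formula.
- **That shared calendar dates add to the problem.** Both arms complete the initial assessments at the same time, so date effects common to both arms largely cancel.

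**Conclusion.** The point holds conditionally. The Aim 2 model named in the protocol does not allow for workshop group in a partially nested design. For any positive ICC the standard error of the RT-waitlist difference is too small. At an assumed ICC of 0.05 and a two-sided 5% level, the true SE is 1.08 to 1.15 times the one reported, and the test rejects a true null 7.1% to 8.9% of the time. Over ICC 0 to 0.10 the error runs from 5.0% to 12.7%. These figures rest on an assumed ICC and alpha, equal arms and clustering in the RT arm only. The protocol's account of shared leaders and participant-supplied examples makes some correlation plausible, but does not show how large it is. All three primary outcomes are affected and the remedy is simple, so it should be settled before the data are analysed.

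**What to change.** In section 6, replace the Aim 2 ANOVA, for primary and secondary outcomes alike, with a partially nested linear mixed model:

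- **Response:** the post score adjusted for baseline. Alternatives are the change score, or a longitudinal model with a workshop-by-time random effect. The workshop effect must act on change or on the baseline-adjusted post score, for the reason in step 5 of the working.
- **Random effect:** workshop group in the RT arm only, with each waitlist student as a singleton.
- **Residual variance:** allowed to differ by arm.
- **Degrees of freedom:** Satterthwaite or Kenward-Roger.
- **Data:** record a workshop-group identifier for every RT participant. The protocol does not say that this is captured.

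The cost is one paragraph of text, one data field and wider confidence intervals. Over ICC 0.02 to 0.10 the SE grows by about 3% (m = 8, ICC 0.02) to 28% (m = 14, ICC 0.10); for groups of 11 at ICC 0.02 the growth is about 5%. With few workshops the intervals widen further, because the degrees of freedom then depend largely on the number of workshops. With only 3 groups, control of type I error is approximate (5.3%-6.7% in the simulation).
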